### Trial design {8}

The study is an investigator-initiated, multicenter, phase II, double-blind, randomized, placebo-controlled trial with three study arms: acotiamide 300 mg/day, acotiamide 600 mg/day, or a placebo, randomized 1:1:1 and stratified by the institution.

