### Sample size {14}

The primary analysis will be a comparison of treatment outcomes between the acotiamide (the 300 mg/day and 600 mg/day groups will be pooled) and placebo groups. The secondary analysis will be a comparison of treatment outcomes between the 300 mg/day and 600 mg/day groups to investigate the dose–response to acotiamide. Therefore, the sample size will be set based on a comparison between the acotiamide and placebo groups (allocation ratio 2:1).

In the prospective observational study conducted at Kyushu University Hospital, 10 out of 23 participants (43.5%), who answered the upper abdominal symptom questionnaire (Revised F Scale) after 4 weeks of acotiamide administration (300 mg/day), answered “No” to “Do you feel any symptom of food sticking in the chest (grabbing) when you swallow something?” as a question of the symptoms of food sticking in the chest. Although a scale different from the Revised F Scale will be used to evaluate the efficacy of acotiamide in the current trial, we expect that a similar proportion of patients will show an improvement in symptoms of food sticking in the chest after acotiamide administration. Therefore, we assume that 55% of patients in the acotiamide group will show an improvement in the symptom of food sticking in the chest. In contrast, 15% of patients in the placebo group are assumed to show an improvement in their symptoms. Considering the exploratory nature of this clinical trial, 39 patients are needed to reach a power of 80% for a normal approximation to the binomial distribution with a one-sided significance level of 5%. Considering the possibility of one dropout per group, the target number of participants is set to 42 (14 in each group).

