## Statistical methods

### Statistical analysis methods for primary and secondary outcomes {20a}

The analysis of the primary endpoint will be conducted in the full analysis set, which will include all randomized patients who received at least one dose of treatment during the study, data collected after treatment commencement, and adherence to GCP. A one-sided *p*-value < 0.05 will be considered statistically significant. The following closed testing procedure will be used to compare the three groups: the placebo group as the control group, the group with 300 mg/day acotiamide, and the group with 600 mg/day acotiamide.The placebo and acotiamide groups (300 mg/day and 600 mg/day groups will be pooled) will be analyzed using a normal approximation to the binomial distribution test. If the difference is significant, the next step will be followed. Otherwise, the procedure will be terminated.For the acotiamide groups (300 mg/day and 600 mg/day), a normal approximation to the binomial distribution test will be performed.

In addition, regardless of whether significance is observed in 1 and 2 above, the difference in the proportion of patients who improve between the placebo and acotiamide groups and between the two acotiamide groups, and the two-sided 90% confidence interval will be evaluated.

As secondary endpoints are exploratory endpoints, proportions will be analyzed using a normal approximation to the binomial distribution test with the placebo and acotiamide groups. Similarly, the same method will be used to test the 300 mg/day group against the 600 mg/day group. The change from the baseline will be analyzed using analysis of covariance (ANCOVA) with the baseline values, as covariates will be employed to test with the placebo and acotiamide groups. Furthermore, the same method will be applied to test the superiority of the 600 mg/day group over the 300 mg/day group.

SAS software (version 9.4; SAS Institute, Cary, NC, USA) will be used for all analyses.

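### The ANCOVA of pooled acotiamide against placebo puts any difference between the two doses into its error term; a three-arm fit would avoid this for one residual degree of freedom

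*Protocol article*

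**What the plan says.** The trial has "three study arms: acotiamide 300 mg/day, acotiamide 600 mg/day, or a placebo, randomized 1:1:1" (Trial design {8}). Under Sample size {14}, the target is 42 patients, 14 in each arm.

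The section on statistical methods for primary and secondary outcomes {20a} tests the binary primary endpoint in two steps: placebo against the two acotiamide arms pooled, then one dose against the other. Secondary proportions get the same two comparisons. For change from baseline, the section specifies ANCOVA "with the baseline values, as covariates will be employed to test with the placebo and acotiamide groups" and adds that "the same method will be applied to test the superiority of the 600 mg/day group over the 300 mg/day group". It calls the secondary endpoints exploratory and mentions no model with three arms.

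The endpoints concerned, listed under Outcomes {12}, are the changes in DCI, basal LES pressure, food-sticking score, EGJOO–QOL and GSRS.

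**The concern.** The trial is partly meant to learn whether the two doses differ. If they do, a model with one indicator for acotiamide of either dose fits a single mean to two groups whose means are not the same. The spread between those means has nowhere to go but the residual. The estimated acotiamide effect is still right on average, but its standard error is overstated, its interval is too wide and its test loses power. The loss grows with the dose difference.

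The comparison affected is acotiamide against placebo on every change-from-baseline endpoint. With 14 patients per arm, precision that can be recovered by a different model statement is worth having.

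**Working it through.** **1. The plan's own figure.** Sample size {14} states that "39 patients are needed to reach a power of 80" per cent, using a "normal approximation to the binomial distribution with a one-sided significance level of 5" per cent, with 55% responding on acotiamide, 15% on placebo and 2:1 allocation. With pooled variance and no continuity correction:

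- mean proportion = (0.15 + 2 × 0.55)/3 = 0.4167
- n(placebo) = [1.645·√(3 × 0.4167 × 0.5833) + 0.842·√(2 × 0.1275 + 0.2475)]² / (2 × 0.40²) ≈ 12.5, so 13
- 13 + 26 = 39, as stated; power at 13:26 is 81.5%

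The primary sizing is sound and is not touched by this point.

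**2. Inputs for the change endpoints.** From the document: three equal arms and m = 14 per arm. Assumed, because the document gives no figures: baseline–outcome correlation 0.5, common SD 1, and a range of dose effects. The residual SD after baseline adjustment is √(1 − 0.5²) = 0.866.

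**3. Inflation of the error variance by pooling.** Let d be the 600 minus 300 mg/day difference in residual SDs. Each dose mean lies d/2 from the pooled mean, so the unmodelled sum of squares is 2m(d/2)² = m·d²/2 = 7d². The pooled two-group ANCOVA has 42 − 3 = 39 residual df. Hence, to a close approximation,

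expected error-variance ratio = 1 + 7d²/39.

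| Dose gap (SD) | d = gap/0.866 | Variance ratio | SE ratio |
|---|---|---|---|
| 0 | 0 | 1.000 | 1.000 |
| 0.5 | 0.577 | 1.060 | 1.03 |
| 0.8 | 0.924 | 1.153 | 1.07 |

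A simulation at effects of 0.3 SD (300 mg/day) and 1.1 SD (600 mg/day) agrees: the pooled model reports a mean SE of 0.306 against a true sampling SD of 0.287, a ratio of 1.066.

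**4. Power for acotiamide v placebo, one-sided 5%.** Simulated in two independent runs, pooled two-group fit against three-arm fit with contrast (−1, ½, ½):

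| Effects, 300/600 (SD) | Two-group | Three-arm |
|---|---|---|
| 0.5 / 0.5 | 52.2% | 52.1% |
| 0.5 / 1.0 | 81.9%; 80.8% | 83.0%; 82.1% |
| 0.3 / 1.1 | 73.9%; 73.7% | 77.3%; 77.4% |

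The gain is 1.1 to 1.3 points at a 0.5 SD gap and 3.4 to 3.7 points at 0.8 SD. With no effect at either dose, both fits reject in 4.8% of simulated trials. The three-arm fit has 42 − 4 = 38 residual df, one fewer than the pooled fit.

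**5. The 600 v 300 mg/day comparison.** A fit to the two acotiamide arms alone has 28 − 3 = 25 residual df, against 38 in the three-arm model; the one-sided 5% critical t is 1.708 against 1.686. Noncentral-t power is:

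| d (residual SDs) | Two-group | Three-arm |
|---|---|---|
| 0.5 | 36.0% | 36.5% |
| 0.75 | 61.2% | 61.9% |
| 1.0 | 82.3% | 83.0% |

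That is under 1 point here, and about 1 point by simulation. The dose difference is a fitted term in this model, so it never enters the error: the simulated SE is 0.331 at a 0.5 SD gap and 0.330 at 0.8 SD, against 0.329 from the three-arm model at both.

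The three-arm model borrows the placebo variance for this contrast. If the placebo residual SD is half that of the active arms, the one-sided 5% dose test rejects 7.2% to 7.7% of the time (two simulations); if it is 1.5 times, 2.6%. The two-arm fit stays at 4.7% to 4.9%.

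**The case against.** The strongest objection is that the defect is inferred. Section {20a} spells out pooling only for the primary test and never says that the two ANCOVA comparisons are separate fits. They could be contrasts from one model, and the full protocol, which is not shown, may say so. This limits how firmly the point can be put but does not remove it. The ANCOVA sentences repeat the two comparisons of the primary test, which are two-group tests, and nothing suggests a three-arm fit. If one model is intended, a clarifying sentence settles the matter.

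Second, nothing here is invalid. That is right: the estimate has the same target under either fit when arms are equal, type I error is not harmed, and the endpoints are exploratory.

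Third, the larger gain needs a dose gap of 0.8 SD, which no figure in the document supports. That also stands, so the result is a range that starts at zero.

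A reader might go further and infer that the planned 600 v 300 mg/day comparison throws away a third of the data, with a loss that grows with the dose-response, and that one three-arm model would be free for both comparisons. The document and the figures do not support this. The patients left out are on placebo and carry no direct information on the difference between doses; only residual df and precision of the baseline slope are lost. The loss is about 1 point of power and does not grow with the dose gap. Nor is the change free for that contrast, since it requires placebo to share the residual variance and baseline slope of the active arms, which the two-arm fit does not.

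**Conclusion.** The point holds for the acotiamide v placebo ANCOVA only, as a minor efficiency improvement. On the natural reading of {20a}, the standard error is overstated whenever the doses differ: by about 3% at a 0.5 SD gap and 7% at 0.8 SD, or roughly 1 and 4 points of power, with no loss if the doses are equal. These figures assume 14 per arm, a baseline–outcome correlation of 0.5, and equal residual variance and slope across arms.

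For this contrast the three-arm fit behaves like the planned one if placebo variance differs, so the gain brings no new exposure there. For 600 v 300 mg/day the planned two-group ANCOVA is a reasonable choice.

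**What to change.** In section {20a}, state that for each change-from-baseline endpoint the acotiamide v placebo comparison comes from an ANCOVA with randomized arm (three levels) as a factor and the baseline value as covariate. Test the contrast of the average of the 300 and 600 mg/day arms minus placebo. Leave the 600 v 300 mg/day comparison as a two-group ANCOVA on the two acotiamide arms, and say so explicitly.

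The cost is one residual degree of freedom (39 to 38) and one contrast statement in the SAS code. No patients, visits or data are added, and the quantity estimated does not change while the arms are equal in size. If dropout leaves the arms unequal, the contrast weights the doses equally, whereas the pooled fit weights them roughly by arm size; the text should name the equal weighting.

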### Interim analyses {21b}

No interim analysis is planned.

### Methods for additional analyses (e.g., subgroup analyses) {20b}

The subgroup analyses will be performed exploratively using a range of variables.

### Methods in analysis to handle protocol non-adherence and any statistical methods to handle missing data {20c}

For the primary endpoint, missing values for any evaluation of the 7-day at 4 weeks of treatment period 1 will be imputed with the average value for that week. Patients with more than 4 days of missing data in a week will be excluded from the analysis.

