### Intervention description {11a}

#### Pre-treatment observational period

Participants who consented will be examined and observed to confirm their eligibility during the pretreatment observational period. The maximum duration of the pretreatment observational period will be 28 days after obtaining consent. During this period, participants will complete a “symptom diary” for seven consecutive days out of 10 before enrollment. If any of the drugs listed in the concomitant use prohibition had been used, their use will be discontinued after consent has been obtained. After confirmation of eligibility, the participants will be enrolled and randomized 1:1:1 to receive acotiamide 300 mg/day, acotiamide 600 mg/day, or a placebo.

#### Treatment period 1

Participants will take the assigned drugs three times per day before meals for 4 weeks and complete the “application of Medication and Symptom Diary.” Participants will visit the institution after 4 weeks of treatment in period 1 (day 29; validity period: days 28–32) to undergo pre-defined examinations and observations, including HRM and symptom assessment.

#### Treatment period 2

Participants who complete treatment period 1 will take 200 mg/dose of acotiamide three times per day before meals for 4 weeks in an open-label fashion and complete the “application of Medication and Symptom Diary.” Patients will visit the institution after 4 weeks of treatment in period 2 (day 29; validity period: days 28–32) to undergo pre-defined examinations and observations, including HRM and symptom assessment.

However, if IRP is normalized (less than the standard value of IRP set for each HRM instrument) based on the HRM study and the worst value of the symptom of food sticking in the chest is 0 (elimination case) after 4 weeks of treatment in period 1 (day 29; validity period: days 28–32), participants will not proceed to treatment period 2 but will transfer to the post-treatment observational period.

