### Outcomes {12}

#### Primary endpoint measurement

The primary endpoint is the proportion of patients exhibiting an improvement in symptoms of food sticking in the chest after 4 weeks of treatment period 1.

“Looking back on your day, did you have any troubles with symptoms of food sticking when you swallowed?” Patients will respond to the question on the following six levels:0: No symptoms1: I had symptoms but had no troubles.2: I had symptoms and had some troubles.3: I had symptoms and was moderately troubled.4: I had symptoms and was quite troubled.5: I had symptoms and was extremely troubled.

The percentage of patients showing an improvement in symptoms is defined as the percentage of patients whose worst symptom score in the latest week was 0 (no symptoms) or 1 (symptoms but no troubles) out of the six levels and whose score improved by at least two points.

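### Filling missing diary days with the weekly average cannot alter a worst-of-week endpoint, so missing days are in effect ignored and errors on the 0-or-1 criterion run only towards improvement

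*Protocol article*

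**What the plan says.** Under Primary endpoint measurement, the protocol article counts as improved those "patients whose worst symptom score in the latest week was 0 (no symptoms) or 1 (symptoms but no troubles) out of the six levels". As a second condition, the score must have fallen by two points or more. Both conditions must hold.

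The section on non-adherence and missing data {20c} applies to "missing values for any evaluation of the 7-day at 4 weeks of treatment period 1" and says that these "will be imputed with the average value for that week". It then sets the limit: "Patients with more than 4 days of missing data in a week will be excluded from the analysis". Up to four of the seven days may therefore be missing, and three recorded days are enough for a patient to be classified. The article states no other rule for missing days in the primary analysis.

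**The concern.** An average is a sensible fill when the endpoint is a weekly mean. Here the endpoint is a weekly maximum. A value that lies at or below the recorded maximum cannot change it, so the stated imputation looks like a treatment of missing data but does nothing.

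The consequence runs one way. A missing day can hide a score of 2 or more and can never add one. A patient with three recorded days has fewer chances to fail than a patient with seven, yet both are reported as having a worst score for the week. This is the only primary endpoint, in 42 patients tested at one-sided 5%, so a few reclassified patients could matter.

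**Working it through.** **1. The plan's own figure.** Inputs from Sample size {14}: 15% on placebo, 55% on pooled acotiamide, 2:1 allocation, one-sided 5%, 80% power. With the pooled-variance normal approximation:

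- Pooled rate = (0.15 + 2 × 0.55)/3 = 0.4167.
- Placebo n = [1.645 × √(0.4167 × 0.5833 × 1.5) + 0.842 × √(0.15 × 0.85 + 0.55 × 0.45/2)]² / 0.40² = (0.993 + 0.422)²/0.16 = 12.5, rounded up to 13.
- Total = 13 + 26 = 39, or 42 with one dropout per group. This matches the article and is not affected by the present point.

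**2. The imputation has no effect.** For any set of recorded scores, mean ≤ maximum. The worst score after filling therefore equals the worst recorded score. Enumerating all 6⁷ possible weeks with every pattern of one to four missing days (27,433,728 combinations), the fill raised the worst recorded score in none, even with the mean rounded up. It turned a true 0-or-1 week into a failure in none.

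**3. Chance of a wrong pass, days missing at random.** If k of the seven days score 2 or more and m days are missing, all k are hidden with probability C(7−k, m−k)/C(7, m).

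| Days scored ≥ 2 | 1 missing | 2 missing | 3 missing | 4 missing |
|---|---|---|---|---|
| 1 | 14% | 29% | 43% | 57% |
| 2 | 0% | 5% | 14% | 29% |

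This step needs no assumption about how symptoms correlate from day to day.

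**4. Apparent response rates (assumed models).** Treat the design rates as the true probability that all seven days score 0 or 1.

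- Independent days: the rate on r recorded days is p^(r/7).
- Correlated days: each patient has a daily probability of scoring 0 or 1 drawn from a beta distribution with concentration 1 (within-patient correlation 1/(1+1) = 0.5), calibrated to the same seven-day rate.

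| Recorded days | Independent, placebo / acotiamide | Correlated, placebo / acotiamide |
|---|---|---|
| 7 | 15% / 55% | 15% / 55% |
| 5 | 26% / 65% | 18% / 59% |
| 3 | 44% / 77% | 24% / 65% |

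**5. One-sided error of the primary test.** Assume a true rate of 15% in both arms, 28 acotiamide and 14 placebo patients, and the pooled z-test evaluated by exact binomial enumeration. Patients who miss days miss two of seven.

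| Who misses two days | Correlated | Independent |
|---|---|---|
| Nobody | 4.7% | 4.7% |
| All patients in both arms | 4.8% | 5.0% |
| 20% of acotiamide, 10% of placebo | 5.0% | 5.7% |
| 20% of acotiamide, no placebo | 5.3% | 6.7% |
| All acotiamide, no placebo | 7.6% | 18.8% |
| No acotiamide, all placebo | 2.9% | 0.8% |

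In the 20% row, for example, the apparent acotiamide rate is 0.15 + 0.20 × (0.181 − 0.15) = 15.6% with correlated days and 0.15 + 0.20 × (0.258 − 0.15) = 17.2% with independent days.

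Steps 4 and 5 model the 0-or-1 condition only and leave out the two-point condition. If that condition is judged on the weekly worst score, it moves the same way, because a lower week-4 worst score enlarges the improvement.

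**The case against.** The strongest reply concerns size. Treatment period 1 is double-blind, all groups take the same number of tablets at the same times, and the diary is an app with daily alerts whose data can be monitored at any time. Large differences in completion between arms are therefore unlikely. Patients must also have had symptoms for at least a month, so days within a patient will be correlated and the independent-days column is an upper illustration. All of this stands. It limits how often the rule bites, but does not make the rule work, and the article itself allows for up to four missing days.

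A reader might infer that any difference in diary completion between arms inflates the false-positive rate. The calculation does not support that: the error rises only if acotiamide patients miss more days, and the test becomes conservative if placebo patients do. Nor can 18.8% be read as the trial's error rate, since it requires every acotiamide patient and no placebo patient to miss two days, with independent days.

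A reader might also infer that each skipped day makes a given patient improved. It does so only in probability: a classification changes only when the missing days hold all the deciding scores.

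Finally, the average might be taken to mean one across other patients. The wording points more naturally to the patient's own week, and the point does not rest on the other reading.

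**Conclusion.** The point holds. The stated imputation is inert for a worst-score endpoint, and any error on the 0-or-1 criterion favours improvement. That part is arithmetic and rests only on reading the average as the patient's own.

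The effect on the treatment comparison is uncertain, because the article gives no rate of missing diary days. With equal missingness the one-sided error stays at about 5%. With a modest excess on acotiamide (20% against none) it is 5.3% to 6.7%, and only the extreme one-sided case gives 7.6% to 18.8%. These figures assume a true 15% response in both arms and the two models above. Response rates would be overstated in whichever arm has missing days. The flaw is worth correcting because it affects the only primary endpoint and the correction is cheap, not because a large bias has been shown.

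**What to change.** Before unblinding, delete the average imputation for the primary endpoint. Replace it with multiple imputation of each missing daily score as a draw on the 0-5 scale from a model that conditions on the patient's recorded days, then take the worst of seven and apply the responder definition. The draws must be able to exceed the recorded maximum; simply resampling the patient's own recorded scores would repeat the present flaw.

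As a simple conservative check, count as not improved any patient whose recorded scores are all 0 or 1 but who has one or more days missing.

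A completeness cut-off of five days out of seven is not enough by itself. It would classify patients with one or two missing days exactly as the current rule does, and so would leave every two-day row of the error table unchanged.

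The cost is a short change to the text, a little more analysis work, and slightly lower observed response rates. The design inputs do not change, so 39 (42 with dropouts) stands.

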### Criteria for discontinuing or modifying allocated interventions {11b}

In any of the following cases, the clinical trial for the participants will be discontinued:If investigators conclude that the continuation of the study will be difficult owing to the worsening of the primary disease (such as progression to achalasia).If investigators conclude that the continuation of the study will be difficult because of the occurrence of adverse events.If participants request the discontinuation of the clinical trial or withdraw consent.If performing follow-ups with participants will become difficult owing to reasons such as patients no longer visiting the institution.If the following serious deviations from the study protocol are revealed:If participants’ ineligibility is discovered after enrollment.If participants require or continue the administration of a prohibited concomitant drug.If pregnancy is detected.If investigators conclude that the continuation of the clinical trial will be difficult because of other reasons.

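### The missing-diary rule removes early stoppers from the primary responder analysis, so response rates are overstated and the comparison is biased toward whichever arm loses more non-responders

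*Protocol article*

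**What the plan says.** Four parts of the protocol article bear on the point.

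- Statistical analysis methods {20a}: "The analysis of the primary endpoint will be conducted in the full analysis set", a set described as "all randomized patients who received at least one dose of treatment during the study", with the further conditions of some data after treatment start and GCP adherence.
- Missing data {20c}: for the seven diary days at week 4 of treatment period 1, missing days "will be imputed with the average value for that week", but "Patients with more than 4 days of missing data in a week will be excluded from the analysis". A patient therefore needs at least 3 of the 7 days to be analysed.
- Discontinuation criteria {11b}: participation ends for several reasons. They include worsening of the disease, cases where "continuation of the study will be difficult because of the occurrence of adverse events", need for a prohibited drug, withdrawal of consent, loss to follow-up, ineligibility found late, and pregnancy.
- Sample size {14}: 39 patients are needed and 42 are enrolled, to allow for one drop-out in each group of 14.

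The primary endpoint {12} is binary. A patient counts as improved if the worst score in the week is 0 or 1 and the score has improved by at least two points.

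**The concern.** A patient who takes the drug for two weeks and then stops has data after treatment start and so belongs to the full analysis set of {20a}. That patient has seven missing days in week 4, so {20c} takes the patient out of the primary analysis. The set that is named and the set that is analysed differ, and the difference arises after randomization.

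Some of the reasons for stopping, worsening and intolerance above all, are themselves unfavourable outcomes. Removing such patients raises the observed response rate in the arm they leave. If the arms lose them unequally, the comparison shifts toward the arm that loses more. A responder endpoint already has a category for these patients, namely not improved. The affected test is the trial's main one: its significance also decides whether the comparison of 300 mg/day with 600 mg/day is tested under the closed procedure.

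**Working it through.** **1. The plan's own figure.** The inputs from {14} are 15% on placebo, 55% on pooled acotiamide, one-sided 5%, 80% power and a 2:1 ratio. With pooled variance and p̄ = (0.15 + 2 × 0.55)/3 = 0.4167, the placebo number is

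n = [1.645 √(1.5 p̄(1 − p̄)) + 0.842 √(0.15 × 0.85 + 0.55 × 0.45/2)]² / 0.40² = 12.5, rounded up to 13.

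This gives 13 + 26 = 39, and 42 with one more per group. The stated figures reproduce, and they treat drop-outs as absent from the analysis.

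**2. Weight of one patient.** It is 1/28 = 3.6 points in the pooled acotiamide arm and 1/14 = 7.1 points on placebo.

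**3. One-sided error when the arms do not differ.** If d of n patients are removed and all are failures, the rate among those left is p × n/(n − d). The rejection probability of the pooled z-test was enumerated over all binomial outcomes at the reduced sizes. The loss patterns other than the first two rows, and the 30% rate, are assumptions; the protocol gives only one drop-out per group.

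| Failures removed (acotiamide / placebo) | True 15% in both arms | True 30% in both arms |
|---|---|---|
| none | 4.7% | 5.2% |
| 2 / 1 (as planned) | 4.7% | 4.9% |
| 4 / 0 | 5.6% | 9.1% |
| 6 / 0 | 9.7% | 13.7% |
| 0 / 1 | 2.8% | 3.7% |
| 0 / 2 | 2.5% | 2.4% |
| 0 / 3 | 2.4% | 1.8% |

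At a true 15% with 4 (6) acotiamide failures removed, the acotiamide rate reads 0.15 × 28/24 = 17.5% (0.15 × 28/22 = 19.1%).

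Part of the movement is discreteness. At a true 15% with no bias, the error is 3.5% at 24:14 and 5.4% at 22:14. The bias therefore accounts for 3.5% to 5.6% in the first case and 5.4% to 9.7% in the second.

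**4. A single data set.** Suppose 10 of 28 acotiamide and 2 of 14 placebo patients respond, and 4 acotiamide non-responders stop early.

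- Under the exclusion rule: 10/24 = 41.7% against 14.3%, z = 1.75, one-sided p = 0.040.
- With all patients counted: 10/28 = 35.7% against 14.3%, z = 1.45, one-sided p = 0.074.

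The conclusion at 5% depends on the rule.

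**5. Power if drop-outs count as not improved.** With one drop-out per group the rates become 0.55 × 26/28 = 51.1% and 0.15 × 13/14 = 13.9%, analysed at 28:14. Power = Φ[(difference − 1.645 SE₀)/SE₁], where SE₀ uses the pooled rate and SE₁ the separate rates.

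- Exclusion, 26:13: (0.400 − 1.645 × 0.1675)/0.1390 = 0.896, power 81.5%; exact enumeration 81.8%.
- Counted as not improved, 28:14: (0.3714 − 1.645 × 0.1594)/0.1322 = 0.826, power 79.6%; exact enumeration 81.4%.

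By the protocol's own formula, 80% after this change would need 15 per group, or 45 patients. The shortfall at 42 is 0.4 points.

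**The case against.** The strongest reply is that the rule does no harm under the protocol's own expectations. With one drop-out per group the error does not rise, and the trial lasts four weeks, is phase II and calls itself exploratory. Worsening may also be commoner on placebo if the drug works, in which case the rule makes the test conservative. The sample size section already treats drop-outs as non-evaluable, so the exclusion agrees with it. All of this stands, and it limits the size of the point. It does not justify the rule, because the number and balance of early stops cannot be known in advance.

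Some stronger readings are tempting but are not supported:

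- *Only completers are analysed.* The rule keeps anyone with at least 3 of 7 diary days in week 4, including a patient who stops late in that week.
- *Every excluded patient is a treatment failure.* The stopping reasons also include withdrawal of consent, loss to follow-up, late-found ineligibility and pregnancy, and a patient still on treatment may simply not fill in the diary. Counting them all as not improved is a convention and a choice of estimand.
- *The full analysis set is everyone randomized and dosed.* It also requires post-treatment data and GCP adherence.
- *No sensitivity analysis is planned.* A condensed article shown without its analysis plan cannot establish that.

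A reader might also hope that the endpoint's reference to the latest week means the last available week. The missing-data section ties the rule to the seven days at week 4 of period 1, so that reading does not rescue early stoppers.

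**Conclusion.** The concern holds as a defect of a stated rule. Patients who belong to the declared analysis set are removed after randomization, for reasons that can depend on outcome. Response rates are overstated whenever the patients removed are non-responders. On the protocol's assumptions with one failure lost per group, 51.1% would read as 55% and 13.9% as 15%.

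The effect on the test depends on the balance of losses. It is negligible at the planned drop-out, anti-conservative if acotiamide loses more failures, and conservative if placebo does. A reader might infer that the rule favours acotiamide or that the planned error rate is already inflated; the documents support neither. The error rates up to 13.7% rest on assumed one-sided losses of 4 or 6 failures, well beyond the one per group that the protocol expects. The change is still worth making, because in a trial of 42 a few unequal losses can decide the primary result.

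**What to change.** Replace the exclusion sentence in {20c} with wording such as: *In the full analysis set, patients with more than 4 missing diary days in week 4 of treatment period 1, including those who discontinued, are counted as not improved. An analysis that excludes them is a complete-case sensitivity analysis.* Make the change before unblinding.

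The costs are small but not nil. Observed rates become slightly less favourable, and a patient on treatment who merely neglects the diary is also scored as not improved. No patients need be added, but the sample size section should describe the power as about 80% with 42 patients, and say that drop-outs stay in the denominator.
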